**DOT intervention trial ***

Immediate group n=36 *asthma education

Delayed group n=36 *asthma education

Week 0 (baseline)

DOT intervention – free for 6 weeks

Start of DOT intervention for 6 weeks

Assessment: Start DOT intervention for 6 weeks

Assessment: stop DOT intervention

week 6

Assessment: stop DOT intervention

Follow- up assessment

week 12

Follow- up assessment

Follow- up assessment

week 18

Follow- up assessment

week 24

* all participants will have received standard asthma education currently used within the Trust before randomisation

**Intervention**

**Intervention and data collection**

The project will utilise a simple application (app)set up on each participant’s or parent/guardian’s mobile smartphone, tablet, or other device that will allow video capture and transmission of ICS inhaler administration. Before the study intervention period is initiated in a given subject, the participant and/or parents/guardians will be trained in use of the video DOT application and how to upload the videos to a web-based repository. As a general rule, it would be expected that young people greater than 12 years of age will record and upload the video themselves, while parent/guardian assistance will be needed for younger children. All mobile devices will be tested after installation to make sure the Dropbox®([https://www.**dropbox**.com](https://www.dropbox.com))repository connection is active and ready to use.

Usual asthma care for the participant will be adopted throughout the study. Regarding the inhaler use, children aged 5 years or older may administer the medication themselves while a parent/guardian will be responsible for inhaler administration in patients 2 up to 5 years of age. However, parent/guardian administration will be allowed if that is usual asthma care in any age child.

Patients who are enrolled in the study will be randomised into two groups (I-med or D-med) as previously described. Participants or parents/guardians of participants will be asked to capture a DOT video twice daily (morning and evening) on their mobile devices of ICS use by the patient. It will be requested that morning videos occur before 9am on school days and before 11am on weekends and holidays, and evening videos occur between the evening meal and bedtime. In the I-med group, participants will be asked to upload daily video recordings via the internet to a repository for a 6 week period at the start of the study. Participants in the D-med group will be free from DOT for the first 6 weeks of the study and will be asked to carry out their usual therapy management. After that, DOT as described above will be applied for the next 6 weeks.

Researchers will evaluate the DOT uploads daily through their password protected access to the video repository. Children and their parent/guardians also will have access to their own videos within the password protected repository. A research team member will follow up with parents/guardians and/or a participant by telephone if two consecutive days of video uploads are missed. The asthma clinical team (consultant/nurse) providing the usual asthma clinical management will be notified about children identified with poor inhaler technique.

**Outcome measurements**

**Baseline (at study initiation)**

- Participant demographic (age, gender, postcode, household smoking status) and relevant clinical data including laboratory data (e.g. total & specific IgE) and comorbid conditions. (Appendix 7)
- Clinician assessment of asthma severity and degree of disease control, i.e. controlled, partially controlled, or uncontrolled.
- Asthma medication profile and any changes made at clinic visit
- Number of asthma ‘attacks’, oral corticosteroids courses, and emergency attendances over the previous 6 weeks.
- Spirometry measurement; fraction of exhaled nitric oxide (FeNO)
- Self-reported Medication Adherence Report Scale (MARS) for parent/guardian and child if 9 years of age or greater(Appendices 10 & 11) (Horne *et al.,* 1999; Horne and Hankins, 2008)
- Interview-administered Beliefs about Medicines Questionnaire (BMQ) for parent/guardian and child9 years of age or greater (Appendices 12 & 13) (Horne *et al.,* 1999)
- Interview-administered Paediatric Asthma Quality of Life Questionnaire (PAQOLQ)if 9 years of age or greater, or the Paediatric Asthma Caregiver Quality of Life Questionnaire (PACQOLQ) (Appendices 14 & 15) (Juniper *et al.,* 1996)
- Interview-administered Asthma Control Test (ACT) or Childhood Asthma Control Test (C-ACT) (Appendices 16 & 17) (Nathan *et al.*, 2004; Liu *et al.*, 2007)
- Self-reported Centre of Epidemiological Studies Depression Scale (CES-D) completed by parent/guardian. Total scores range from 0 to 60 with a score > 16 representing depressed mood (Appendix 18) (Radloff 1977). A CES-D score indicating depressed mood in the parent/guardian will be reported to their GP.
- ICS inhaler technique

**At 6 weeks**

- Clinician assessment of asthma control
- Asthma medication profile and any changes made at clinic visit
- Number of asthma ‘attacks’, oral corticosteroids courses, and emergency attendances since baseline visit.
- Spirometry measurement; FeNO.
- Self-reported MARS
- PAQOLQ/PACQOLQ and ACT/C-ACT
- ICS inhaler technique

**At 12 weeks**

- Clinician assessment of asthma control
- Asthma medication profile and any changes made at clinic visit
- Number of asthma ‘attacks’, oral corticosteroids courses, and emergency attendances since baseline visit.
- Spirometry measurement; FeNO.
- Self-reported MARS
- PAQOLQ/PACQOLQ and ACT/C-ACT
- ICS inhaler technique

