**Study design**

A randomised intervention trial will be used. Participants will be randomised to either an immediate (I-med) or a delayed (D-med) mobile technology DOT intervention. Randomisation will be restricted based on two factors including age (categorized as Young Children ages 2 up to 5 years, Children ages 5 up to 12 years and Young People ages 12 up to and including 16 years) and patient gender (Gore, 1981).

Both subject groups will receive standard-of-practice asthma education and management in the Asthma Clinic prior to study enrolment. Participants allocated to the I-med group will take part in the mobile technology DOT intervention for the first 6 weeks. Outcomes will be evaluated at the start (week 0) and end of the 6 week intervention period and during clinic visits at weeks 12 and 18 for follow-up. Those participants allocated to the D-med group will have the DOT intervention started after a 6 week “intervention-free” interval with usual Asthma Clinic care. Outcomes in the D-med group will be assessed at baseline (week 0), week 6 (intervention start), week 12 (end of intervention), and at weeks 18 and 24 for follow-up. (see Figure 1)

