**(c) Sample size calculation**

The variability in quality of life (QOL) score changes in a similar population was reported in a pilot study to be 1.3 units (Young *et al.*, 2001). To have an 80% power to detect a statistically significant (P<0.05; two-tailed Student t-test) difference for effect of the intervention between groups of 1 QOL unit would require 36 children per group.

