**Data analysis**

Statistical analyses will be conducted by the researcher after entering all data into SPSS (IBM SPSSv.23, USA). All nominal data collected during the study will be analysed using descriptive approaches. Group differences (I-med and D-med groups) will be studied using the independent sample Student t-test. If the data are not normally distributed non-parametric statistics will be utilised (Mann-Whitney U test for independent group differences). A paired Student t-test will be used to detect any differences associated with the study periods within each group

Adherence to ICS use in participants will be determined based on the patients’ general practitioner records of medicine prescribed and the patients’ records of medicine dispensed within the 6 week period, monitoring of video submissions, as well as the total scores achieved from the MARS questionnaires.

Categorical variables associated with non-adherence will be analysed using Chi-squared analysis. If the expected frequency falls below 5, the Fisher’s exact test will be employed.

Factors that affect the adherence to ICS inhaler use will be determined using patient demographic and clinical data together with responses obtained through administration of BMQ, CES-D, MARS, PACQOLQ/PAQOLOQ and ACT/C-ACT questionnaires to the participants and participants’ parents/guardians as appropriate. Multiple regression analysis will be performed to evaluate the relative contribution of different predictors to non-adherence.

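### Attack, oral steroid and emergency counts cover 6 weeks at baseline and week 6 but 12, 18 and 24 weeks at later visits, so paired comparisons of the counts as recorded would use unequal exposure times

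*Protocol*

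**What the plan says.** Under Outcome measurements, the baseline list asks for the number of asthma attacks, "oral corticosteroids courses, and emergency attendances over the previous 6 weeks". The lists for weeks 6, 12, 18 and 24 (the last for D-med only) repeat one wording: attacks, "oral corticosteroids courses, and emergency attendances since baseline visit".

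Under Study design, each phase lasts 6 weeks. I-med has DOT in weeks 0-6 and follow-up visits at weeks 12 and 18. D-med is free of DOT in weeks 0-6, has DOT in weeks 6-12, and has follow-up visits at weeks 18 and 24.

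Under Data analysis, the within-group plan is: "A paired Student t-test will be used to detect any differences associated with the study periods within each group". It is stated for all outcomes together. It does not name the event counts and says nothing on rates, person-time or subtracting one visit's count from the next.

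**The concern.** The follow-up wording suits week 6, where looking back to baseline gives the same 6-week window as the baseline item. At weeks 12, 18 and 24 the same wording makes the count cumulative, while baseline stays a 6-week count.

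Two consequences follow if the recorded values go straight into the paired test. A comparison with baseline sets 12, 18 or 24 weeks of events against 6. And in D-med the week-12 value adds the DOT-free weeks to the DOT weeks, so the comparison of week 12 with week 6, which should set DOT against no DOT in the same children, cannot show improvement. A real benefit on exacerbations could be reported as harm.

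**Working it through.** The protocol gives no event rate and no expected count for this item, so there is no stated figure to reproduce. The one design figure used is the group size: the sample size section concludes that a "difference for effect of the intervention between groups of 1 QOL unit would require 36 children per group". I take n = 36 per group as given.

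**Step 1: windows and expected counts.** Let λ be the mean number of events per child per 6 weeks, constant over time (no true change).

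| Visit | Window | Expected count | Ratio to baseline |
|---|---|---|---|
| Baseline | 6 weeks before | λ | 1 |
| Week 6 | weeks 0-6 | λ | 1 |
| Week 12 | weeks 0-12 | 2λ | 2 |
| Week 18 | weeks 0-18 | 3λ | 3 |
| Week 24 (D-med) | weeks 0-24 | 4λ | 4 |

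For the mean not to rise against baseline, the average rate since baseline must fall by at least 1 − 1/2 = 50% (week 12), 1 − 1/3 = 67% (week 18) or 1 − 1/4 = 75% (week 24).

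**Step 2: D-med, week 12 against week 6.** The week-12 count is the week-6 count plus events in weeks 6-12. With consistent reporting it cannot be lower in any child. If DOT halves the rate, the expected week-12 count is λ + 0.5λ = 1.5λ against λ at week 6.

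Steps 1 and 2 need no value for λ.

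**Step 3: false worsening in the paired t-test.** Assumptions: λ from 0.1 to 1.0; Poisson counts, either with the same rate in every child or with gamma variation between children (variance 1); no true change; n = 36; 20,000 simulated trials. Entries are the percentage of trials with a significant rise (nominal upper tail 2.5%), without / with between-child variation.

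| λ | Week 12 v baseline | Week 18 v baseline | Week 24 v baseline | Week 12 v week 6 |
|---|---|---|---|---|
| 0.1 | 16 / 15 | 45 / 42 | 73 / 67 | 42 / 35 |
| 0.25 | 39 / 37 | 85 / 81 | 98 / 97 | 95 / 89 |
| 0.5 | 67 / 62 | 99 / 98 | 100 / 100 | 100 / 100 |
| 1.0 | 93 / 90 | 100 / 100 | 100 / 100 | 100 / 100 |

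Hand check at λ = 0.5, week 12 against baseline, no between-child variation: the mean difference is 2λ − λ = 0.5, its variance per child is 2λ + λ = 1.5, and its standard error is √(1.5/36) = 0.204. The expected t is 0.5/0.204 = 2.45 against a critical value of 2.03, which gives about 66%. The simulation gives 67%.

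Week 6 against baseline, where the windows match, gives about 2-3% at every rate.

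**Step 4: true benefit in D-med.** If DOT halves the rate (same rate in every child), week 12 against week 6 as recorded shows significant worsening in 9%, 58%, 95% and nearly 100% of trials at λ = 0.1, 0.25, 0.5 and 1.0.

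**Step 5: equal windows.** With 6-week interval counts (week 12 minus week 6) and no true change, a significant rise appears in about 2-3% of trials at every assumed rate.

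**The case against.** There is a good deal to say for the plan, and most of it stands.

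- **The phase data are not lost.** A reader might infer that D-med's DOT period cannot be recovered. It can: the item is recorded at every visit, so week 12 minus week 6 gives it. A SAP, which may exist, could specify this. But subtraction needs both visits and consistent reporting (an early attack left out at a later visit can make an interval count negative), and the protocol does not call for it.
- **The faulty test is one reading.** A reader might infer that the plan commits to testing cumulative counts against baseline. The paired test is generic and does not name these counts; its reference to study periods would also fit counts per phase.
- **The randomised comparison is safe.** At week 6 I-med has had DOT, D-med has not, and both count 6 weeks. Comparisons between groups at weeks 12 and 18 also have equal windows and are not inflated, though by then both groups' counts mix DOT and non-DOT time, which blurs the contrast.
- **These counts are not a named key endpoint.** Objective 3 and the Outcomes measure section do not list them; at most they fall under clinical assessment of asthma control. The sample size rests on quality of life.
- **A cumulative count can fall against baseline.** The baseline window precedes the visit and is not part of later counts. A child with 3 attacks before baseline and 1 in the next 12 weeks shows a fall. The never-lower property holds only between follow-up visits.
- **The constant rate is an assumption.** Children enter while partially controlled or uncontrolled, so rates may fall after baseline by regression to the mean, which would offset some of the inflation.
- **Recall is a lesser point.** The protocol does not say that families are the source of these counts, and GP and pharmacy records give a separate check on steroid courses.

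What remains is that the protocol itself fixes the counting window, and as written that window does not match the 6-week phases it means to compare.

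**Conclusion.** The mismatch of windows is real: 6, 6, 12, 18 and 24 weeks. Used as recorded in a paired comparison, the counts at weeks 12, 18 and 24 are expected at 2, 3 and 4 times baseline under a constant rate, and D-med's week-12 count cannot fall below its week-6 count. These statements do not depend on the event rate; the second assumes consistent reporting.

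How often a trial would declare false worsening does depend on it. Over the assumed 0.1 to 1.0 events per child per 6 weeks the range is 15-93% at week 12, 42-100% at week 18 and 67-100% at week 24 against baseline. A reader might infer that false worsening is certain, or that the trial's main result is biased. The documents support neither: the low end of the range is far from certainty, the error arises only if the counts are compared without subtraction or a rate, and the randomised week-6 comparison is unaffected. I rate this a moderate issue on a supporting clinical outcome.

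**What to change.** At weeks 12, 18 and 24, count attacks, steroid courses and emergency attendances *since the last study visit*. Alternatively, keep the wording and state that interval counts are derived by subtracting successive visits. In either case, compare events per 6-week phase and allow for the actual days between visits. A missed visit merges two phases under either wording, so the length of each interval needs recording. A Poisson or negative binomial model with a time offset is a suitable option, not a requirement.

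The cost is one phrase in three visit lists, and in the data collection form if it carries the same wording (Appendix 7 is not shown). No visit is added, the reporting window shortens to about 6 weeks, and cumulative totals can still be obtained by adding the intervals.

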**At 18 weeks**

- Clinician assessment of asthma control
- Asthma medication profile and any changes made at clinic visit
- Number of asthma ‘attacks’, oral corticosteroids courses, and emergency attendances since baseline visit.
- Spirometry measurement; FeNO.
- Self-reported MARS
- PAQOLQ/PACQOLQ and ACT/C-ACT
- ICS inhaler technique

**At 24 weeks (D-med group only)**

- Clinician assessment of asthma control
- Asthma medication profile and any changes made at clinic visit
- Number of asthma ‘attacks’, oral corticosteroids courses, and emergency attendances since baseline visit.
- Spirometry measurement; FeNO.
- Self-reported MARS
- PAQOLQ/PACQOLQ and ACT/C-ACT
- ICS inhaler technique

**At study end (both groups)**

- GP prescribing records for the 12 months leading up to, and during the study time period
- Community pharmacy dispensing records for the 12 months leading up to, and during the study time period

Clinician assessment of participant asthma severity will be defined according to accepted guidelines and asthma control will be categorized as uncontrolled, partially controlled, or controlled (BMT/SIGN 2012). Data regarding the medication profile will include any respiratory or allergy drugs added or removed, existing drug dosage changes, and drugs initiated for respiratory infections.

Patient inhaler technique will be evaluated by reviewing each video from the first 2 days of the intervention period and then a sample (at least one weekly) of the videos that have been uploaded to the repository application. The presence/absence of every required video will be documented.

Inhaler technique will be assessed and categorized on a three-point scale as effective, partially effective or poor (Patterson *et al.*, 2005). Inhaler technique evaluation will be based on criteria relevant to the child’s inhaler manufacturer administration directions, such as removal of cover, priming of device, vigorous shaking before each actuation, respiratory expiration before actuation, and holding of breath after inspiration. Effective technique will be recorded when the participant meets all relevant criteria. Partially effective technique will be recorded when errors in technique are observed but it is thought that the participant would receive some medication. Poor inhaler technique will be recorded when critical errors in technique occur such that it is considered unlikely that any medication would be inhaled (Patterson *et al.*, 2005; Melani *et al.*, 2011).

Adherence will be calculated based on total number of videos submitted during the 6 week intervention divided by the number of days during which DOT monitoring has occurred.

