**Outcomes measure**

The primary outcome measures in this pilot study concern two areas. Firstly, the feasibility, practicality, and persistence of using a mobile DOT approach in the management of asthma in children and young people will be assessed by evaluation of ICS inhaler technique and monitoring inhaler use adherence. Secondly, asthma control associated with the mobile DOT approach will be assessed with clinical (including number of patients who progress to controlled category) and laboratory disease assessment, participant-reported medication adherence, and quality of life measurements (PAQOLQ/PACQOLQ and ACT/C-ACT).

Secondary outcome measures for the study include any impact of mobile DOT on participants’ inhaler technique and adherence. These two aspects of asthma management will be assessed by comparisons between intervention groups and within groups during, and across, phases of the study. Participant and parent/guardian factors that influence the impact of the DOT method on inhaler use and adherence also will be determined.

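### Inhaler technique is scored from stored DOT videos with no masking to date or clip order, so rater expectation could contribute to an apparent early-to-late improvement within the DOT phase

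*Protocol*

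**What the plan says.** **Which clips are scored.** Protocol, Outcome measurements, At study end (both groups): "Patient inhaler technique will be evaluated by reviewing each video from the first 2 days of the intervention period and then a sample", the sample being "at least one weekly) of the videos that have been uploaded to the repository application".

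**The scale.** The same section says: "Inhaler technique will be assessed and categorized on a three-point scale as effective, partially effective or poor". The effective grade requires every relevant criterion from the device directions to be met. The middle grade is defined thus: "Partially effective technique will be recorded when errors in technique are observed but it is thought that the participant would receive some medication". The poor grade applies where inhalation of any medication is judged unlikely.

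**Who looks at the clips, and when.** Intervention and data collection says: "Researchers will evaluate the DOT uploads daily through their password protected access to the video repository". The same team contacts families: "A research team member will follow up with parents/guardians and/or a participant by telephone if two consecutive days of video uploads are missed". Clinic staff in turn "will be notified about children identified with poor inhaler technique". Under Data protection, only researchers can open all the files, which are held under study ID.

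**How the scores are used.** Outcomes measure lists evaluation of technique under the primary feasibility outcome, and the impact of DOT on technique as a secondary outcome. The latter is assessed by "comparisons between intervention groups and within groups during, and across, phases of the study". Data analysis plans paired tests within each group.

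The protocol mentions no masking of the technique score, no shuffled order, no second rating and no separate rater.

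**The concern.** The people who watch uploads day by day will usually know which child they are seeing, how far into DOT the child is, how earlier clips looked and whether the clinic was alerted. If the same viewing produces the outcome score, a rater who has seen poor early clips and knows that the clinic was told has reason to expect later clips to look better.

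Where a grade depends on opinion, that expectation can move the score. The during-phase comparison sets early clips against late clips, so a drift in the rater and a real improvement in the child look the same.

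This is a matter of design and conduct, not of analysis. If the only scores are made with the date known, no analysis can restore the masking afterwards. Because the clips are stored, technique on video is one of the few outcomes in this open trial that could be scored with the date hidden at little cost.

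**Working it through.** The protocol gives no figure on this point, so there is none to reproduce. The check has three parts.

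**1. Does the text lead to unmasked scoring?**
- The scoring section names neither a rater nor a time of rating.
- The intervention section has researchers evaluate uploads daily, and poor technique is reported to the clinic. Some judgement of technique is therefore made in real time, by people who know the child and the day.
- Data protection gives no one outside the research team access to all files.
- No other reviewer appears. Unmasked scoring by the team running DOT is the natural reading, but it is an inference.

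**2. Which comparisons can video scores reach?**
- The D-med group has no videos in weeks 0 to 6, and none are planned in follow-up for either group.
- The planned between-group and across-phase comparisons must therefore use the inhaler technique item recorded at clinic visits (weeks 0, 6, 12 and 18, and week 24 for D-med).
- Only the early-versus-late comparison within the DOT phase rests on the videos.

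**3. How large could the effect be?** This is an illustration.

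From the protocol: 36 children per group (Sample size calculation), tested within each group (Data analysis).

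Assumed, not in the documents: 40% of clips truly effective at both times; no true change; latent early-late correlation 0.6; every child supplies an early and a late clip; a fraction *q* of late clips that are less than effective is upgraded to effective; exact McNemar test at two-sided 0.05.

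Spurious gain in the proportion rated effective = *q* × (1 − 0.40):
- *q* = 0.10: 0.10 × 0.60 = 6 points
- *q* = 0.20: 0.20 × 0.60 = 12 points
- *q* = 0.30: 0.30 × 0.60 = 18 points

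Simulated false-positive rates (repeat runs differ by about a point):

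| Upgrade rate *q* | Spurious gain | n = 36 (one group) | n = 72 (groups pooled) |
| --- | --- | --- | --- |
| 0 | 0 points | 2% | 3% |
| 0.10 | 6 points | 5% | 10–11% |
| 0.20 | 12 points | 15–16% | 31–33% |
| 0.30 | 18 points | 32–33% | 65–66% |

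The n = 36 column matches the planned within-group analysis.

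A second illustration uses the paired t-test that the protocol names, on the three-point score. It assumes 20% poor, 40% partially effective and 40% effective, a random one-category rating error in 10–30% of clips, and an upgrade of one category for a fraction *q* of non-effective late clips. At n = 36 it rejects about 4–5% of the time with no upgrading, and 8–12%, 17–29% and 33–53% at *q* = 0.10, 0.20 and 0.30.

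**The case against.** **The judgement wording sits at the other boundary.** The opinion-based phrases separate partially effective from poor. Effective is a checklist grade, whereas the McNemar illustration moves clips across the effective line. This stands as a limit on that illustration. Deciding from home video whether shaking, breathing out or breath-holding was adequate still takes some judgement, and the t-test illustration allows upgrades at both boundaries.

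**The rater is not named.** A reader might infer that the protocol assigns the outcome scoring to the staff delivering DOT. It does not say so. Daily evaluation of uploads may be largely a log of which videos arrived, and a later masked rating is not forbidden. What stands is narrower: no masking is planned, and no other reviewer is mentioned.

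**The size depends on invented upgrade rates.** This stands. At a 10% upgrade rate and n = 36, the McNemar test rejects about 5% of the time, which is no more than the nominal level. A reader might quote the pooled n = 72 figure of about 66%, but the protocol tests within each group, so that figure does not describe the planned analysis.

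**Only one comparison is affected.** A reader might infer that the trial's whole case on technique, or its randomised comparison, is compromised by the video scoring. The documents do not support that: those comparisons rest on clinic-visit ratings. The early-versus-late video change has no control group, so even with masked scores it could not be attributed to DOT alone. Alerts and follow-up may also genuinely improve technique.

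**Conclusion.** The point holds in a limited form. The protocol scores a partly judgement-based outcome from stored clips without masking to date, order or earlier ratings, and the only reviewers it mentions check uploads daily while running DOT. Rater expectation could therefore contribute to an apparent early-to-late improvement in the within-group, during-phase comparison. The documents do not show that it would, or by how much.

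Under the stated assumptions the size runs from negligible (false-positive rate about 5% at a 10% upgrade rate) to material (about 32% and 18 points at a 30% upgrade rate), against 2% with none. The conclusion that the scoring should be masked does not depend on these figures. It rests on the reading that daily reviewers would also supply the outcome scores, which the text suggests but does not state. The change is worth making because it is cheap, not because a serious bias has been shown.

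**What to change.** Leave the daily unmasked check in place for alerts. In the technique paragraph under At study end (both groups), state that the outcome score for the first-2-day clips and the sampled weekly clips:
- is assigned after the child's DOT period has ended;
- is made in random clip order, with date and earlier ratings hidden;
- is given by existing researchers, where possible one who did not review that child's uploads (team size is not stated, so a separate reader should not be a requirement);
- is the score used for the during-phase comparison.

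**Cost.** Two videos a day for 2 days is 4 clips; with about 6 weekly clips this makes about 10 per child. 10 × 72 = 720 clips, or 12 hours at an assumed 1 minute each. Limiting the set to the first-2-day clips and one final-week clip gives 5 × 72 = 360 clips, or 6 hours. No extra visits are needed.

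**What it leaves open.** Raters may still recognise a child. Clinic-visit technique ratings, and so the between-group and across-phase comparisons, are not protected. Late I-med clips and early D-med clips both fall near week 6, which may invite a direct comparison. That would be a new analysis, setting I-med children still uploading after about six weeks against D-med children newly trained in filming. It should be left out or labelled exploratory.

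### Video adherence is total clips divided by days, so it is a videos-per-day index rather than a proportion, and a surplus clip can offset a missed dose slot

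*Protocol*

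**What the plan says.** The Protocol, under Intervention and data collection, sets the schedule. Families are "asked to capture a DOT video twice daily (morning and evening) on their mobile devices of ICS use by the patient", and the timing asked for is: "morning videos occur before 9am on school days and before 11am on weekends and holidays, and evening videos occur between the evening meal and bedtime". For the immediate group the task is to "upload daily video recordings via the internet to a repository for a 6 week period"; the delayed group does the same six weeks later.

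Under Outcome measurements, At study end (both groups), two statements bear on how the videos are scored:

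- A record by required video: "The presence/absence of every required video will be documented".
- The adherence formula, whose numerator reads "Adherence will be calculated based on total number of videos submitted during the 6 week intervention". The denominator is in days, since the same sentence has this count "divided by the number of days during which DOT monitoring has occurred".

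The formula has no limit of two clips per day, does not tie a clip to a morning or evening slot, and has no rule for repeated or late clips. Data analysis lists the video count as one of several adherence sources, alongside prescribing and dispensing records: "monitoring of video submissions, as well as the total scores achieved from the MARS questionnaires".

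**The concern.** The numerator and denominator are in different units. Videos are due twice a day, but the total is divided by days. A reader who takes the result as a proportion will read one filmed dose a day as complete adherence. The Background cites average inhaled-steroid adherence in children of about 50%, and 93.3% median observed adherence in a mobile DOT pilot in sickle cell disease. The index as defined cannot be set beside either figure without rescaling.

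A second weakness would survive a change of denominator. Because the count is of submissions rather than slots covered, an extra clip in one slot makes up arithmetically for an empty slot elsewhere. The slot record that would prevent this is described in the same section, but the formula does not use it.

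Inhaler-use adherence is part of the feasibility component of the primary outcome (Outcomes measure), and non-adherence is the dependent variable of the planned multiple regression (Data analysis). An unambiguous definition therefore matters for both.

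**Working it through.** The protocol states no expected adherence value or video count, so there is no figure of its own to reproduce. The check is direct arithmetic.

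**Inputs from the protocol**
- Intervention period: 6 weeks × 7 = 42 days.
- Videos requested per day: 2.
- Slots: 2 × 42 = 84, taking every day as monitored.

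**Inputs assumed** (not in the protocol)
- Share of slots filmed, *c*.
- Share of filmed slots with a second clip, *e*.

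**Formulas**
- Protocol index = clips / days = 84 × *c* × (1 + *e*) / 42.
- Clips over slots (only the denominator changed) = 84 × *c* × (1 + *e*) / 84.
- Slot-based adherence = slots with at least one video / 84 = *c*.

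**Step 1: denominator, no surplus clips (*e* = 0)**
- All slots filmed: 84/42 = 2.0; slot-based 84/84 = 100%.
- One slot a day filmed: 42/42 = 1.0; slot-based 42/84 = 50%.

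This factor of 2 follows from the stated formula and schedule alone.

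**Step 2: numerator, with surplus clips**

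| Slots filmed (*c*) | Second clip (*e*) | Clips | Protocol index | Clips / 84 | Slot-based | Excess (points) |
|---|---|---|---|---|---|---|
| 60% | 0% | 50.4 | 1.20 | 60% | 60% | 0 |
| 60% | 5% | 52.9 | 1.26 | 63% | 60% | 3 |
| 60% | 20% | 60.5 | 1.44 | 72% | 60% | 12 |
| 70% | 5% | 61.7 | 1.47 | 73.5% | 70% | 3.5 |
| 70% | 25% | 73.5 | 1.75 | 87.5% | 70% | 17.5 |

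The excess in points is 100 × *c* × *e*, so it is exactly zero when *e* = 0.

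**Step 3: limiting case**

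A child filmed every evening with two clips and never in the morning submits 42 × 2 = 84 clips. The protocol index is 84/42 = 2.0, the same as full compliance, although 42/84 = 50% of slots were covered. This is a constructed extreme that shows what the formula cannot distinguish; it is not a forecast.

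**Step 4: what each change repairs**

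Dividing clips by 84 repairs the scale but leaves the excess in Step 2. Counting each slot once but still dividing by days removes the excess but leaves the 0-to-2 scale. Counting slots over slots repairs both and cannot exceed 100%.

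**The case against.** The strongest reply is that the protocol asks for one video per administration, twice a day, and nowhere describes repeated, make-up or per-puff clips. The telephone call after two days in a row without uploads does not invite replacement videos. Since the presence or absence of each required video is recorded, the count in the formula may be meant as the count of required videos received. De-duplication is also the kind of detail often left to a later document. Adherence is further drawn from prescribing and dispensing records and MARS, so the video count does not stand alone.

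Much of this stands. It means surplus clips are a possibility and not a documented event, and that the rates in the table are assumptions. It does not remove the point, because the protocol itself states the formula, and as worded it counts submissions and divides by days. The denominator problem needs no surplus clips at all.

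A reader might infer more than the text allows:

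- *That adherence is overstated and the primary result inflated.* Not shown. With no surplus clips the numerator error is nil.
- *That the net error is upward.* Surplus clips push the count up, but doses taken and not filmed, or uploads that fail, push it down. The protocol gives no basis for the net direction.
- *That the error is largest in partial non-adherers.* Nothing in the protocol supports this.
- *That the day-based denominator distorts group comparisons or the regression.* If every participant has the same number of monitored days, dividing by 42 instead of 84 is a constant factor of 2. It changes the reported level and its interpretation, but not the ordering of participants.

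**Conclusion.** The point holds in a limited form. What is certain is that the stated formula gives a videos-per-day index: 2.0 for full compliance and 1.0 for half, given two videos a day over 42 monitored days. What is conditional is the overstatement from surplus clips: zero if none are uploaded, and about 3 to 12 points at 60% coverage if 5% to 20% of filmed slots carry a second clip. Both the coverage and the clip rates are assumed. This is a minor defect in a stated rule. It is worth correcting because the data needed are already to be recorded.

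**What to change.** In Outcome measurements, At study end (both groups), replace the adherence sentence with a slot-based definition, for example:

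*Video adherence is the number of scheduled morning and evening slots with at least one video, each slot counted once from the presence/absence record, divided by the number of slots scheduled in the participant's 6-week intervention period (2 per day, normally 84). A video recorded outside the requested window still counts for its slot; the number of such videos is reported separately.*

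The last sentence is needed because the windows are only requests and the evening one has no clock limits. Without it, an observed but late dose could be scored as missed. Using scheduled slots as the denominator also settles which days count as monitored, which the present wording leaves open.

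The cost is a short change of text and no new data collection. The small downside is that the reported adherence may be slightly lower than a raw clip count would give.
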